## Abstract

**Background:**

Although cardiovascular disease has decreased, there is still potential for prevention as obesity and diabetes increase. Exercise has a positive effect on many cardiovascular risk factors, and it can significantly reduce the components of metabolic syndrome. The main challenge with exercise in primary care is how to succeed in motivating the patients at risk to change and increase their exercise habits. The objective of this study is to modify the cardiovascular risk in middle-aged men, either through a health promotion intervention alone or combined with an exercise intervention.

**Methods/design:**

During a two-year period we recruit 300 men aged from 35 to 45 years with elevated cardiovascular risk (> two traditional risk factors). The men are randomized into three arms: 1) a health promotion intervention alone, 2) both health promotion and exercise intervention, or 3) control with usual community care and delayed health promotion (these men receive the intervention after one year). The main outcome measures will be the existence of metabolic syndrome and physical activity frequency (times per week). The participants are assessed at baseline, and at 3, 6, and 12 months. The follow-up of the study will last 12 months.

**Discussion:**

This pragmatic trial in primary health care aimed to assess the effect of a health promotion programme with or without exercise intervention on cardiovascular risk and physical activity in middle-aged men. The results of this study may help to plan the primary care interventions to further reduce cardiovascular mortality.

The study was registered at the Controlled Trials (
http://www.controlled-trials.com). Trial number: ISRCTN80672011. The study received ethics approval from the Coordinating Ethics Committee at Helsinki University Hospital on 8 June 2009 (ref: 4/13/03/00/09).

## Background

Cardiovascular diseases continue to be among the most important causes of mortality, especially in men. In Finland, the North Karelia project is a success story of effective health promotion to reduce cardiovascular risk
[1]. From a public health perspective, exercise is one the most effective means of reducing the risk of cardiovascular diseases. Exercise is a key modifiable factor either alone or in combination with other lifestyle changes and treatments to reduce hypertension and elevated cholesterol levels. The effectiveness of exercise has been shown in weight loss
[2], particularly when combined with dietary changes. Exercise also decreases the incidence of type 2 diabetes mellitus in high risk groups (people with impaired glucose tolerance or the metabolic syndrome)
[3]. There is also evidence that exercise improves the metabolic syndrome in general
[4] and reduces HbA1c levels in patients with type 2 diabetes
[5].

There is a lot of interest in cardiovascular risk reduction in primary care and many interventions are nurse-based
[6,7]. Many communities in Finland have recently adopted health examinations by public health nurses for 40-year-old men to improve their lifestyle habits. Although the effectiveness of such interventions may now be questionable
[8], at the planning stage of this project it was essential to include a nurse-based intervention. At the Kirkkonummi Health Center, we decided to combine a randomized controlled trial at the onset of such a health promotion project. The trial was approved by the municipality authorities.

A major challenge in health behavior changes is the maintenance of the adopted lifestyle
[9]. An individual approach may not be sufficient for change. A group-based exercise intervention may motivate the participants to continue with their new exercise habits
[10]. In addition to the health promotion intervention by a nurse, we included a group exercise intervention to increase the effectiveness of the intervention.

We aimed to develop an exercise intervention model for primary care that increases the physical activity of middle-aged men with increased cardiovascular risk. A randomized controlled trial was carried out to study the effects of this intervention. We also aimed to establish cooperation between a health center and other municipal activities, namely adult education and exercise services in health promotion of middle-aged men. The aim of this randomized controlled trial is to investigate the effects of this intervention on participants’ metabolic syndrome and physical activity.

## Objectives

The main aim of the study is to assess the effect of the interventions on physical activity and metabolic syndrome in middle-aged men, having at least two cardiovascular risk factors at the beginning of the trial.

The effect of the intervention on the individual risk factors of metabolic syndrome (overweight, waist circumference, blood cholesterol level, high-sensitivity C-reactive protein (hs-CRP)), on the physical activity factors (self-reported physical activity, and 2 km walking test), and body constitution as measured by InBody® are also examined.

## Methods/design

### Study design

The study is a three-arm one-center randomized controlled trial (Figure 
1). Two methods of health promotion are studied in middle-aged men with elevated cardiovascular risk. After screening and randomization, one study group receives a 1½-hour health promotion intervention by a public health nurse. The other intervention group receives, in addition to public health nurse intervention, a guided group exercise intervention of 12 weeks. The third group is randomized to serve as a control and men in this group may participate in the intervention after one year, should they wish to.

**Figure 1 F1:**
[figure not shown]
Study design and flow chart.

### Ethics approval

The study received ethics approval from the Coordinating Ethics Committee at Helsinki University Hospital on 8 June 2009 (ref: 4/13/03/00/09). All participants receive both oral and written participant information and are asked to give written informed consent.

### Recruitment and time schedule

We recruite men aged 35 to 45 years with at least two cardiovascular risk factors. They are recruited to the project in three ways: 1) by invitation letter to the 40-year-old age cohort, 2) by identifying high-risk group of men within health services (targeted opportunistic screening), and 3) by informing about the project in the media and on the Internet.

The study protocol was accepted in 2009 and recruitment of study subjects and randomization started in 2010.

#### Inclusion criteria

▪ Age 35–45 years

▪ At least two cardiovascular risk factors as follows:

- BMI 27–34 kg/m^2^

- Waist circumference > 94 cm

- Fasting glucose >6.1 mmol/l

- Total plasma cholesterol >4.0 mmol/l

- LDL-cholesterol > 3.0 mmol/l

- Triglycerides >2.0 mmol/l

- Systolic blood pressure > 140 mmHg

- Diastolic blood pressure > 90 mmHg

- Currently either :

• Smoking

• On cholesterol-lowering medication

• On blood pressure-lowering medication

#### Exclusion criteria

– BMI over 34 (or any other physical barrier preventing participation in the exercise intervention)

– Active exerciser (exercising at least 30 minutes 3 times a week or more)

– Having an immediate health problem requiring treatment or a severe risk factor; for example, recently diagnosed or uncontrolled type I diabetes, or a symptomatic coronary artery disease.

### Study interventions

In addition to study interventions, all groups receive, if necessary, standard treatment at Kirkkonummi Health Center, a municipal public primary care unit. If a participant shows any need of medical treatment, or his medications required medical attention, he is referred to a primary care physician.

### Health promotion intervention by nurse

Public health nurses use standard practices in their health promotion intervention. Before onset of the trial they receive education from the Finnish Heart Association. The nurses use the type 2 diabetes disease risk assessment form (Finnish Diabetes Association), and cardiovascular risk assessment (the Finnish Heart Association). The intervention includes assessment of individual risks, dietary habits, physical activity and a motivational talk about the habits. The intervention lasts up to 90 minutes and does not include follow-up.

If the men have elevated blood sugar, total plasma cholesterol over 7.0 mmol/l, uncontrolled hypertension or another reason for medical assessment, the nurse referres the patient to a physician for consideration of medication.

### Exercise intervention

In addition to the health promotion intervention, the other group is invited to a group exercise intervention. The size of the teaching groups is from 10 to 20 people. The exercise intervention is guided by a physical education counselor and consists of basic physical training. The exercise sessions each last 60 minutes. During the 12 weekly meetings several safe and moderately strenuous exercise activities are carried out, such as Nordic walking, fitness circle, volleyball, swimming, circuit training, gym, boxing, zumba, etc.

The exercise intervention aims at creating a comfortable atmosphere that encourages safe and regular physical training. Another aim is form groups of men that might continue exercising together.

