### Sample size

Sample sizes were calculated by statistical power analysis. We hypothesised that the percentage of men continuing the increased exercise level after one year would be 30% in the control group and 50% in the exercise group. To detect this difference with α = .05 and β = .80, 91 men in each group are needed.

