### Statistical analysis

A primary intention-to-treat analysis will be carried out. The main analyses involve standard two-sample comparisons (parametric or non-parametric depending on the distribution of the data) looking at effect sizes at 3 and 12 months.

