## Discussion

In this study, we assess the effects of primary care interventions aiming to reduce cardiovascular risk in early middle-aged men. Health promotion by public health nurses has become a popular method in cardiovascular prevention. Its effectiveness has, however, recently been questioned
[4]. At the onset of this the trial, it was clear that it had to be included it in the intervention. We also wanted to study an exercise intervention, as many cardiovascular risk factors can be controlled through exercise
[12,13].

We chose a group-based intervention because we considered the social support in the group to be an important motivational factor for the success of the intervention. Kirkkonummi is a suburban municipality, where most of the families move from other parts of Finland to work in the capital region. Many men do not have the social networks of their youth for maintaining their exercise activities. One possible result of this trial is that men continue to exercise in their intervention groups. We will follow-up for the potential societal effects of the trial using qualitative methods.

The strengths of this study are that it is a primary care pragmatic trial and that the results are readily generalizable to similar primary care settings. Also, the interventions included are feasible and non-expensive. If they prove effective, they can easily be transferred to other similar circumstances.

The study has some limitations as well. Blinding is not feasible and this study is performed as an open trial. Randomized controlled trials are not common in primary care health centers and there are threats to validity, e.g. how to guarantee similar processes by all study nurses and how to avoid other protocol violations. A special challenge is to keep the participants in the control group. As the participating men are not patients but working-aged and busy, their participation in the outcome measurements is a challenge.

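### The exercise arm is treated in classes of 10 to 20 men, but the sample size and the named two-sample comparisons treat every man as independent

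*Protocol article*

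**What the plan says.** The protocol article's Randomization section allocates men individually, from a list transferred to numbered sealed envelopes. Under Exercise intervention, only the combined arm attends weekly classes over 12 weeks: "The size of the teaching groups is from 10 to 20 people". The same section adds: "Another aim is form groups of men that might continue exercising together". The Discussion gives the reason for choosing groups: "we considered the social support in the group to be an important motivational factor".

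The Sample size section assumes that the proportion keeping up the increased exercise level at one year "would be 30% in the control group and 50% in the exercise group", and concludes: "To detect this difference with α = .05 and β = .80, 91 men in each group are needed". It mentions no ICC or design effect. The Statistical analysis section says: "The main analyses involve standard two-sample comparisons", parametric or not according to the distribution. It does not mention class. The abstract sets recruitment at 300 men in three arms.

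**The concern.** Classmates share an instructor, a programme and a group that is itself meant to motivate. If the group works as the authors hope, a class that holds together raises its members' later exercise jointly, and a class that dissolves lowers it jointly. A test that assumes independence would count such a class as 10 to 20 separate results.

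The comparison at stake is the one the trial was sized for, exercise against control, together with exercise against health promotion alone. Two different harms are possible, and they belong to different analyses. Left unadjusted, the test rejects a true null too often. Adjusted, it is valid but has less power than the Sample size section states. If class membership is not recorded during the trial, the adjustment may not be possible later.

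**Working it through.** **Inputs from the protocol article.** Rates 30% and 50%; α = 0.05; 91 per group (Sample size). Class size m = 10 to 20 (Exercise intervention). 300 men in three arms (abstract), so 100 per arm if allocation is equal. The article prints β = .80; it is read here as power 0.80, because taking it literally gives about 16 per group. A two-sided test is assumed.

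**Assumed.** ICC 0.01, 0.05 and 0.10; full classes; clustering in the exercise arm only.

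**Step 1: the plan's own figure.** The variances are 0.3 × 0.7 = 0.21 and 0.5 × 0.5 = 0.25. Then n = (0.21 + 0.25)(1.960 + 0.842)²/0.20² = 90.3, rounded up to 91. This reproduces the stated number exactly with independent men, so it contains no design effect. (The pooled-variance formula gives 93.)

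**Step 2: design effect in the exercise arm.** DEFF = 1 + (m − 1) × ICC.

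**Step 3: type I error of the unadjusted test.** With equal arms and equal total variance, the true standard error is r = √[(1 + DEFF)/2] times the one used, and the type I error is 2[1 − Φ(1.960/r)]. For ICC 0.05 and m = 15: DEFF = 1.70, r = √1.35 = 1.162, 1.960/1.162 = 1.687, giving 9.2%.

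**Step 4: large-sample power of a class-adjusted test.** SE = √[(0.21 + 0.25 × DEFF)/n] and power = Φ(0.20/SE − 1.960). For ICC 0.05, m = 15, n = 91: SE = √(0.635/91) = 0.0835, 0.20/0.0835 = 2.394, and Φ(0.434) = 67%. With n = 100: SE = 0.0797 and power = 71%.

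| ICC | m | DEFF | Type I error, unadjusted | Power, adjusted, 91 per arm | Power, adjusted, 100 per arm |
|---|---|---|---|---|---|
| 0.01 | 10 | 1.09 | 5.5% | 78% | 82% |
| 0.01 | 15 | 1.14 | 5.8% | 77% | 81% |
| 0.01 | 20 | 1.19 | 6.1% | 76% | 80% |
| 0.05 | 10 | 1.45 | 7.7% | 71% | 75% |
| 0.05 | 15 | 1.70 | 9.2% | 67% | 71% |
| 0.05 | 20 | 1.95 | 10.7% | 63% | 67% |
| 0.10 | 10 | 1.90 | 10.4% | 64% | 68% |
| 0.10 | 15 | 2.40 | 13.3% | 56% | 60% |
| 0.10 | 20 | 2.90 | 16.0% | 51% | 54% |

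Simulating the t-test at ICC 0.05 gives 7.2%, 8.9% and 10.5%, within about half a point of the formula. Pooled-variance power is about one point lower throughout.

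**Step 5: few classes.** The table uses normal quantiles. At 91 per arm there are only 91/20 = 4.6 to 91/10 = 9.1 classes. With Satterthwaite degrees of freedom at ICC 0.05, power at 91 per arm falls to about 67%, 59% and 51% for classes of 10, 15 and 20.

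**Step 6: break-even at 100 per arm.** Large-sample power stays at 80% while DEFF is at most (0.20² × 100/2.802² − 0.21)/0.25 ≈ 1.20. That is an ICC of 0.20/9 = 0.022, 0.20/14 = 0.014 or 0.20/19 = 0.010 for the three class sizes, with nobody lost.

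**The case against.** The strongest reply is that the size of the effect is unknown. The documents give no ICC, and they say only that the groups might continue together. At an ICC near 0.01 the unadjusted type I error is about 6% at most, and 100 analysed men per arm still give about 80% large-sample power. This stands, and it is why the range starts at 0.01. It does leave no reserve for loss, and the Discussion itself calls participation in outcome measurement a challenge.

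Full classes are also an upper bound. Men are invited, the analysis is by intention to treat, and non-attenders and men lost to follow-up reduce the effective class size. This stands too. It works in the opposite direction to the small-sample loss in Step 5.

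A reader might infer that type I error certainly exceeds 5%. The documents do not support that. If the classes affect nobody, individual randomisation keeps the ordinary test valid however the men are later grouped. Inflation needs class effects that are real but average to zero.

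A reader might also infer that the plan as written suffers both harms in full. It does not. The unadjusted test at 100 per arm keeps power of roughly 75% to 82%, and its main fault is type I error. The loss of power belongs to the adjusted test.

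Nor is the whole trial affected. Health promotion alone against control involves no classes, and the social mechanism is argued for continued exercise, so the case is weaker for metabolic syndrome. The power figures concern the 30% against 50% proportion, not the primary outcome of exercise times per week.

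Finally, model details commonly sit in an analysis plan that is not shown. But the article is not silent: it names an analysis and prints a sample size, and both assume independence.

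**Conclusion.** The point holds in conditional form. The sample size and the named analysis ignore the classes in one arm, while the protocol's own rationale gives reason to expect correlated outcomes there. Any positive ICC makes unadjusted standard errors too small for exercise against either other arm. The consequence ranges from minor at ICC 0.01 to serious at 0.10, as tabulated. These figures depend on the assumed ICC, full classes, equal allocation and a two-sided test, and the power figures are large-sample values. The documents do not establish that the trial is underpowered by any particular amount.

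**What to change.** - Record class membership for every man in the exercise arm.
- For exercise times per week, replace the two-sample comparisons involving the exercise arm by a partially nested linear mixed model: a random class effect in that arm only, arm-specific residual variances, and Satterthwaite or Kenward-Roger degrees of freedom.
- For metabolic syndrome, use a method suited to a binary outcome with few clusters. Examples are a logistic model with a class effect in the exercise arm, or a cluster-robust risk difference, with a small-sample correction. A logistic model has no separate residual variance to estimate, so the linear specification cannot simply be carried over.
- Restate the power for exercise against control with an assumed ICC and its range, at the planned number per arm.

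The cost is one extra variable, revised analysis wording and a lower stated power. Restating the power does not restore it. At ICC 0.05, 80% large-sample power would need (0.21 + 0.25 × DEFF) × 2.802²/0.20² = 113, 125 or 137 men per arm for classes of 10, 15 or 20. Whether to accept the lower power or recruit more is for the sponsor to decide.

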### Control group

The participants of the control group receive both the health examination and the exercise intervention after the 12-month follow-up, if they so wish.

### Outcome measures

The outcomes are measured after 3, 6 and 12 months of the randomization. The blood tests are taken at months 0, 3 and 12. Other outcomes are measured by Internet surveys and, if the participant does not respond, by telephone surveys.

Primary outcome measures will be 1) metabolic syndrome defined by International Diabetes Federation/American Heart Association
[11], thus fulfilling three or more of the following criteria:

- systolic blood pressure ≥ 130 or diastolic blood pressure ≥ 85 or specific medication;

- triglyserides ≥1.7 mmol/L or specific medication;

- HDL cholesterol < 1.0 mmol/L or specific medication

- fasting plasma glucose ≥ 5.6 mmol/L or specific medication;

- waist circumference >94 cm

2) and self-reported physical activity measured by how many times per week a participant performs vigorous exercise activity. Table 
1 shows also the secondary outcome measures.

**Table 1 T1:** Outcome measures

**Variable**	**T0**	**T1**	**T2**	**T3**
1. Primary outcome measures				
1.1 Metabolic syndrome1 (yes/no)	x	x	x	x
● Blood pressure, waist circumference,				
● Blood LDL- and HDL-cholesterol, triglycerides, blood glucose				
1.2 Physical activity	x	x	x	x
● Self-reported physical activity, exercise times, per week				
2. Other outcome measures				
● 2 km walking test (s)	x	x		x
● Self-reported general health (0–100)	x	x	x	x
● Self-reported overall stress (0–100)	x	x	x	x
● Utilisation and costs of medical services	x	x	x	x
● Individual cardiovascular risk factors: total cholesterol (mmol/L), LDL-cholesterol (mmol/L), HDL-cholesterol (mmol/L), smoking (yes/no), blood glucose (mmol/L), hs-CRP (mmol/L)	x	x	x	x
	x	x		x
● Body composition (InBody): muscle mass (kg), body fat mass (kg)	x	x		x

1 Defined by International Diabetes Federation/American Heart Association
[11].

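### The metabolic syndrome outcome counts drug treatment as a criterion met, and the nurse session under test can prompt drug treatment, so comparisons with control are open to bias against the active arms

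*Protocol article*

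**What the plan says.** All references are to the Protocol article.

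- **Outcome measures.** Metabolic syndrome is a yes/no primary outcome, "thus fulfilling three or more of the following criteria". Four criteria carry a medication alternative. The blood pressure line reads "systolic blood pressure ≥ 130 or diastolic blood pressure ≥ 85 or specific medication". The line on triglycerides has the same form, "triglyserides ≥1.7 mmol/L or specific medication". So does the line on HDL, "HDL cholesterol < 1.0 mmol/L or specific medication". The glucose line completes the four: "fasting plasma glucose ≥ 5.6 mmol/L or specific medication". Waist circumference is the only criterion that rests on measurement alone. The definition is attributed to a cited source.
- **Health promotion intervention by nurse.** The triggers for referral are raised blood sugar, total cholesterol above 7.0 mmol/l, and "uncontrolled hypertension or another reason for medical assessment, the nurse referres the patient to a physician for consideration of medication".
- **Study design** and **Control group.** Both active arms receive the nurse session after randomisation. Controls may have it once their 12 months of follow-up are complete.
- **Study interventions.** For every arm: "If a participant shows any need of medical treatment, or his medications required medical attention, he is referred to a primary care physician".
- **Randomization.** Baseline measurements come before allocation.
- **Statistical analysis.** Two-sample comparisons at 3 and 12 months, by intention to treat.

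**The concern.** One component of the randomised intervention can prompt an event (starting a drug) that the primary outcome scores as a criterion met. Controls do not receive that component until the outcome window has closed. If more men start drugs in the active arms than in the control arm, the outcome moves against the active arms, even where measured blood pressure or glucose has improved.

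What is at stake is how the comparison with control is read. A null result could mean that the programme changed nothing. It could also mean that the programme lowered measured risk while the medication clause kept treated men classified as cases. The outcome as defined cannot tell these apart.

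**Working it through.** **1. Can a drug start hold a man in the positive class?** Take a man who meets the waist, blood pressure and glucose criteria and neither lipid criterion: 3 of 5, positive. He is referred, starts a blood pressure drug, and his reading falls below the threshold. By measurement he now meets 2 of 5 (negative). As scored he still meets 3 of 5 (positive). This holds on any reading of the word *specific*, since a drug prescribed for blood pressure belongs to the blood pressure line. The same applies to glucose.

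The clause decides the outcome only when exactly two of the other four criteria are met. That is C(4,2) = 6 of the 2^4 = 16 patterns of those four. This counts patterns, not men.

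**2. Can a drug start make a man positive?** Total cholesterol triggers referral but is not one of the five criteria. Suppose a man has waist 98 cm, LDL 5.2, HDL 1.4, triglycerides 1.4, blood pressure 125/80 and glucose 5.3. His total cholesterol is about 5.2 + 1.4 + 1.4/2.2 = 7.24 mmol/l, above the trigger. He meets 1 criterion (waist).

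- If a lipid drug is scored on neither lipid line: 1 of 5, no change.
- If it is scored on both: 3 of 5, a new case with no value worse.

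Of all 32 patterns, 6 turn from negative to positive if the drug counts for triglycerides only, and 12 if it counts for both lipid lines. This route depends wholly on how *specific* is read.

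**3. Does it differ by arm?** Let m be the share of men in an arm who are positive only because of a drug started after randomisation. Then

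scored prevalence = measured-value prevalence + m,

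and the difference between arms shifts by e = m(active) − m(control). Drugs present at baseline do not enter e. Men may join partly on the ground of "On cholesterol-lowering medication", but randomisation balances this in expectation. The article gives no rate of medication starts, so e cannot be derived from it.

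**4. What would a given e do?** The article's only sizing figure concerns exercise, not metabolic syndrome. It reproduces: (0.3×0.7 + 0.5×0.5) × (1.960 + 0.8416)² / 0.2² = 0.46 × 7.849 / 0.04 = 90.26, so 91 per group. I borrow that 91 for the outcome here and **assume** 50% metabolic syndrome in control and 30% in an active arm by measured values. With scored prevalences p1 = 0.50 and p2 = 0.30 + e, d = p1 − p2, p̄ their mean and n = 91:

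power = Φ{ [d√n − 1.960√(2p̄(1−p̄))] / √(p1(1−p1) + p2(1−p2)) }.

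For e = 0.05: d = 0.15, p̄ = 0.425, and [0.15×9.539 − 1.960×0.6991] / 0.6910 = 0.088, so power is 53.5%.

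| Assumed e (points) | Observed difference (points) | Power at 91 per group | n per group for 80% power |
|---|---|---|---|
| 0 | 20 | 79.1% | 93 |
| 2 | 18 | 69.8% | 117 |
| 5 | 15 | 53.5% | 170 |
| 10 | 10 | 27.2% | 388 |

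(The 93 in the first row uses the pooled variance; the unpooled form gives the article's 91.) Assumed control rates of 40% and 60% give a similar pattern. With no true effect and control at 50%, e = 10 points would appear as a 10-point harm, significant in 27.2% of trials.

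**5. Which comparisons are touched?** Each active arm against control is exposed. Nurse-only against nurse-plus-exercise is less affected, because both arms receive the session. The physical activity primary outcome is not affected.

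**The case against.** The strongest reply is that starting a drug is not reserved to the active arms. Every group has access to standard treatment and to referral when need appears. Baseline blood pressure, glucose and lipids are measured before allocation, and blood is drawn again at months 3 and 12 in all arms, so a raised value in a control can be acted on. Referral leads only to a physician's judgement. The exclusion of men with an immediate problem or a severe risk factor also removes some likely drug starters. All of this stands, and it is why e may be small or zero. It does not make the arms alike, because the dedicated assessment of up to 90 minutes, with its named triggers, is described only as part of the nurse session.

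The second reply is that counting treated men as still affected is a defensible choice. It belongs to the definition that the article cites, and it avoids crediting a drug's effect to a lifestyle programme. That also stands: the clause is not an error in itself. The difficulty is that the outcome as defined then shows only one side of the trade-off.

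Third, supportive analyses are often left to an analysis plan, which is not shown here. The tension itself, however, lies between two statements that the article makes.

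A reader might infer that one lipid prescription does create new cases. The documents do not support that. The word *specific*, repeated line by line, more naturally means a drug for that line's abnormality, and with one centre there are no sites to differ in reading it.

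**Conclusion.** The point holds as an exposure to bias. A man who starts a blood pressure or glucose drug after referral cannot lose that criterion, and the session that prompts referral is withheld from controls until after the 12-month outcome. The direction is against the active arms. The size is the net between-arm difference in men who are positive only through drugs started after randomisation. It cannot be derived from the article, and zero is within its range. The power figures above rest on assumed prevalences and an assumed e, and show sensitivity only.

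Two stronger readings should be resisted. A reader might conclude that the outcome *is* biased by some definite amount; without medication-start rates, no such amount can be stated. A reader might also conclude that the trial cannot speak to cardiovascular risk at all. That goes too far: measured cholesterol fractions, glucose, smoking and hs-CRP are separate outcomes, the comparison between the two active arms is less affected, and physical activity is untouched.

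**What to change.** Keep the defined metabolic syndrome outcome as primary. Add one pre-specified supportive version at months 3 and 12, along these lines: *a criterion is met through medication only if the drug was in use at T0; for drugs started after randomisation, the measured value alone decides.* Record drug and start date at the visits already planned, tabulate medication starts by arm, report both versions side by side, and interpret each comparison with control in the light of both.

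The cost is one medication item (scoring the outcome already needs medication data), one extra analysis and one table. The downside is two versions to report. The supportive version credits drug effects to the programme, which is why it should stand beside the primary and not replace it. This concerns scoring and reporting only; no change to referral or treatment is implied.
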